**Aim 2. Sleep characteristics and psychiatric symptom profiles**					
2a. Sleep profiles in patients with mental disorders	Patients with mental disorders	Identify latent profiles integrating sleep symptoms.	Clustering features: Sleep measures (e.g., ISI, RU-SATED), External validators: EQ-5D-5L, SWLS	Dimension reduction: Uniform manifold approximation and projection Clustering: Density-Based Spatial Clustering of Applications with Noise, hierarchical clustering, k-means, Gaussian mixture models Group comparisons across profiles: one-way ANOVA with Tukey’s HSD (if assumptions met) or Kruskal–Wallis test with Steel–Dwass post-hoc tests for continuous variables; chi-square tests for categorical variables.	Exploratory
2b. Sleep profiles in patients with diabetes	Type 1 and type 2 diabetes	Identify latent profiles integrating sleep symptoms.	Clustering features: same as 2a External validators: EQ-5D-5L, SWLS	Same as 2a, plus between-group comparisons of profile distributions and validators	Exploratory
2c. Psychiatric profiles in patients with developmental disabilities	Patients with developmental disabilities	Identify latent profiles integrating psychiatric symptoms.	Clustering features: Psychiatric symptoms (e.g., PHQ-9, GAD-7) External validators: EQ-5D-5L, SWLS	Same as 2a	Exploratory
**Aim 3. Attitudes toward digital health technology**					
3a. eTAP-J validation	Patients with mental disorders, healthy participants	Examine the reliability and validity of the Japanese version of the eTAP.	Target instrument: eTAP-J Validation measures: eHEALS	Structural validity: CFA Convergent and discriminant validity: correlation Factors influencing the intention to use psychological support delivered via digital technologies: mediation analysis or SEM	Confirmatory
3b. ASSURE-HT, ASSURE-AI validation	Patients with mental disorders	Examine the reliability and validity of ASSURE-HT and ASSURE-AI.	Target instruments: ASSURE-HT (15 items) and ASSURE-AI (15 items) Validation measures: prior AI/face-to-face therapy experience	Structural validity: CFA Internal consistency: Cronbach’s *α* and *ω* (evaluated separately for ASSURE-HT and ASSURE-AI) Known-groups validity: score differences by prior treatment/therapy experience (ASSURE-HT and ASSURE-AI analyzed separately) Differences in attitudes by demographic variables (age group, sex): ANOVA or regression; Chi-square test or ordinal logistic regression (depending on outcome scale type)	Confirmatory
3c. Ethical concerns about romantic relationships with AI	Patients with mental disorders	Examine to what extent patients with mental disorders consider ethical concerns about romantic relationships with AI.	Predictor: anthropomorphism Mediators: relationship authenticity, desire for real-world relationships with AI Outcome: fulfilment of emotional needs	Correlations, serial mediation	Confirmatory

Abbreviations: ANOVA, Analysis of variance; CFA, Confirmatory factor analysis; DU3STEP, Three-step approach for distal outcomes in latent class/profile analysis; EFA, Exploratory factor analysis; FDR, False discovery rate; LPA, Latent profile analysis; SEM, Structural equation modeling; *α*, Cronbach’s alpha; *ω*, McDonald’s omega; QOL, uality of Life; DQ5-J, Distress Questionnaire; PHQ-9, Patient Health Questionnaire-9; GAD-7, Generalized Anxiety Disorder-7; EQ-5D-5L, EuroQoL 5 Dimensions 5-Level; BPBs, Brief Parental Burnout Scale; SES, Subjective Socioeconomic Status (Childhood and Current); K6, six-item Kessler Psychological Distress Scale; AQ-28, Autism Spectrum Quotient; ASRS, Adult ADHD Self-Report Scale; ISI, Insomnia Severity Index; RU-SATED, Regularity, Satisfaction, Alertness, Timing, Efficiency, Duration of Sleep Scale; SWLS, Satisfaction With Life Scale; SAP, Shift-and-Persist coping strategy; MCQ-30, Metacognitions Questionnaire; CAS-1R, Cognitive Attentional Syndrome Scale-1 Revised; EC, Effortful Control Scale; HSD, Honestly Significant Difference; eTAP-J, Japanese version of the e-Therapy Attitudes and Process Questionnaire; eHEALS, eHealth Literacy Scale; ASSURE-HT and ASSURE-AI, Attitudes toward Safety, Support, Understanding, and Risk for Human-AI therapists; AI, artificial intelligence.

#### 2.5.1 Aim 1: Psychosocial Correlations and Measurement Foundations for QOL and Psychiatric Symptoms

The registry will examine the reliability and validity of the DQ5-J and conduct cross-sectional association analyses to investigate how BPBs, SAP, SES, and metacognitive beliefs and coping strategies (MCQ-30 and CAS-1R) are associated with the QOL and psychiatric symptoms measures. For the analyses, we will employ standard correlational and multivariable modeling approaches as well as perform the exploratory profiling of coping strategies.

#### 2.5.2 Aim 2: Sleep Characteristics and Psychiatric Symptom Profiles

The registry will identify data-driven profiles integrating the sleep characteristics and/or psychiatric symptoms measures in individuals with mental disorders and examine their associations with QOL and symptom severity. The same profiling pipeline will be applied to participants with type 1 and type 2 diabetes as well as those with developmental disabilities.

#### 2.5.3 Aim 3: Attitudes Toward Digital Health Technology

The registry will evaluate the measurement properties of the instruments assessing attitudes toward and ethical concerns about digital health technology in the mental health domain, including the eTAP-J and ASSURE scales (ASSURE-HT, ASSURE-AI). In addition, ethical concerns about romantic relationships with AI will be examined given their potential influence on the acceptance of and engagement with emerging digital health interventions.

### 2.6 Sample Size and Sampling

Because this is a registry-based observational study, the study size will primarily be determined by the inclusion of as many feasible participants as possible within prespecified diagnostic strata, consistent with the survey company’s prior recruitment performance. A pragmatic target of 200–300 participants per group will be set, yielding an overall enrollment target of 3000–3300 participants. To contextualize this range, 200–300 participants per stratum corresponds approximately to 95% confidence-interval half-widths of ± 6.9% to ± 5.7% for proportions near 0.50, detectable standardized mean differences of *d *≈ 0.28 to 0.23 for two-group comparisons, and detectable correlations of *r *≈ 0.20 to 0.16. For more complex structural equation modeling and person-centered analyses, adequacy depends strongly on the model complexity, measurement quality, class separation, convergence, and stability; accordingly, these analyses will be interpreted primarily using model fit, convergence, and stability criteria, and disease-specific profiling analyses will be undertaken only if sufficient sample sizes are obtained [34].

Because online surveys tend to disproportionately attract younger respondents, age-stratified quota sampling will be employed to ensure adequate representation across age groups. Minimum quotas will be set at 20 participants per group for each age decade in the 20s (including ages 18 and 19), 30s, 40s, and 50s, and at least 10 participants per group for individuals aged 60 years and older. These quotas will be applied flexibly in groups with limited numbers of registered panel members.

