**Methods and Analysis::**

We will conduct a nationwide registry-based cross-sectional study in Japan. Participants will include adults with mental disorders, those with physical conditions, and healthy participants, recruited through an online survey company. After providing electronic consent, all participants will complete an online survey providing information on demographics, diagnoses, and treatment. The registry will also capture information on Quality of Life (QOL) as well as related psychosocial factors, psychiatric symptoms, sleep characteristics, and attitudes toward digital health technology. Data collection is planned for March 2026, with a target enrollment of 3300 participants. Planned analyses will validate patient-reported instruments and characterize how these variables are related to QOL.

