### 2.2 Participants

Participants will be recruited in March 2026 from a nationwide web-based research panel managed by Macromill, Inc. (Tokyo, Japan). Recruitment will be conducted through direct invitations and study announcements posted on the Macromill website. The Macromill panel has been used in several previous studies [38,39]. Participants will be recruited using prespecified eligibility criteria and stratified quotas by diagnostic category. The provider maintains both general-population and disease-specific subpanels, including pre-identified panelists who have received physician diagnoses of the target disorders at medical institutions. Diagnostic classification will be based on the participant-reported history of physician diagnosis recorded in Macromill’s disease-specific panels, in which disease information is updated annually. By way of confirmation, invitees will additionally complete a screening item upon starting the survey to confirm their current diagnosis; diagnoses will not be independently verified through medical records or structured diagnostic interviews. Only respondents who pass their confirmation stage will proceed to the survey.

Inclusion criteria will be as follows: (1) understanding the study purpose and providing informed consent; (2) registration in a pre-identified disease-specific panel comprising individuals who have received a physician diagnosis of a target disorder and a positive response to an upfront screening item confirming a current diagnosis of one of the following conditions: major depressive disorder, social anxiety disorder, panic disorder, post-traumatic stress disorder, obsessive/compulsive disorder, insomnia, attention-deficit/hyperactivity disorder, autism spectrum disorder, type 1 diabetes, and type 2 diabetes; or registration as a healthy individual based on self-report indicating no current physician-diagnosed disease; (3) age ≥18 years; and (4) ability to respond in Japanese. Exclusion criteria will include the inability to provide informed consent or complete the survey.

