### 2.7 Statistical Analysis

To minimize information bias, we will conduct logic and range checks during data cleaning. Descriptive analyses will summarize distributions, floor and ceiling effects, and reliability indices. Unless otherwise specified, analyses will use two-sided tests, apply pre-specified multiple comparison correction strategies that differ by sub-study (see **Supplementary Materials**), and control for prespecified covariates (e.g., age and sex). Prespecified subgroup comparisons and corresponding interaction tests for diagnostic strata and sex will be conducted a priori, whereas other interaction analyses will be considered exploratory. Effect sizes with 95% confidence intervals will be reported, including Cohen’s *d *and Hedges’ *g* for continuous outcomes, odds ratios from logistic regression models, and standardized *β* coefficients for regression paths. Because the panel provider supplies only complete records for both the survey and the two-week retest, analyses will be restricted to complete-case data. Additional methodological details are provided in the **Supplementary Materials**.

In Sub-study 1a of Aim 1, all the analyses will be conducted in accordance with the Consensus-based Standards for the selection of health Measurement Instruments (COSMIN) guidelines [87]. The psychometric validation of the DQ5-J will include CFA to test the a priori unidimensional structure, with EFA reserved as a follow-up if the model fit is inadequate, internal consistency indices (Cronbach’s alpha and McDonald’s omega), test–retest intraclass correlation coefficients, model fit criteria, hypothesis-driven convergent and discriminant validity testing, and receiver operating characteristic analyses.

In Sub-studies 1b–1d of Aim 1, the correlations between the psychosocial factors and QOL/psychiatric symptoms will be examined by assessing the associations among the BPBs scores, SAP, SES, the psychiatric symptoms and sleep characteristics measures, and QOL using correlation analyses, linear regression models, and logistic regression. Sub-study 1d will additionally apply multiple-group structural equation modeling with moderated mediation and latent profile analysis to characterize the coping strategies assessed by the CAS-1R [88,89,90].

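### Section 2.6: 200–300 participants in each of 11 groups gives 2,200–3,300 overall, so the stated lower bound of 3,000 does not follow

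*Protocol article*

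**What the plan says.** The sample-size section (2.6) sets one range per group and derives the total from it: "A pragmatic target of 200–300 participants per group will be set, yielding an overall enrollment target of 3000–3300 participants".

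The groups are defined by the inclusion criteria in section 2.2. The diagnoses are "major depressive disorder, social anxiety disorder, panic disorder, post-traumatic stress disorder, obsessive/compulsive disorder, insomnia", followed by "attention-deficit/hyperactivity disorder, autism spectrum disorder, type 1 diabetes, and type 2 diabetes". The alternative route of entry is "or registration as a healthy individual based on self-report indicating no current physician-diagnosed disease". Section 2.2 also says that quotas are stratified by diagnostic category. The populations in Table 1 are all formed from these groups and add no further one.

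The abstract gives a single figure, "with a target enrollment of 3300 participants".

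Section 2.6 then describes what the 200–300 range delivers within a stratum: half-widths of 6.9% to 5.7% for a proportion near one half, d of about 0.28 to 0.23, and r of about 0.20 to 0.16.

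**The concern.** The sentence presents the total as the product of the per-group range, so a reader will multiply by the number of groups. The upper end works and the lower end does not. Two minimum targets then stand in one sentence, 200 per group and 3,000 overall, and with 11 groups they are different requirements.

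What is at stake is the benchmark for recruitment. If every group stopped at 200, each per-group target would be met and the overall target would be missed by 800. A later report could call the same enrolment a success or a shortfall, depending on which figure it cites. No analysis is at stake.

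**Working it through.** **Inputs**
- Groups: 6 diagnoses in the first part of the section 2.2 list, 4 in the second part, and 1 healthy group, so 6 + 4 + 1 = 11.
- Target per group: 200–300 (section 2.6).
- Overall target: 3,000–3,300 (section 2.6); 3,300 (abstract).
- Inflation for incomplete records: none stated. Section 2.7 says that the panel provider supplies complete records only.

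**Step 1. Reproduce the total.** Total = number of groups × target per group.
- Upper end: 11 × 300 = 3,300. This agrees with section 2.6 and the abstract, and supports the count of 11.
- Lower end: 11 × 200 = 2,200, against the stated 3,000. The difference is 800, which is 800/2,200 = 36% of the computed figure.

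**Step 2. Try other group counts.**

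| Groups | × 200 | × 300 |
|---|---|---|
| 9 | 1,800 | 2,700 |
| 10 | 2,000 | 3,000 |
| 11 | 2,200 | 3,300 |
| 12 | 2,400 | 3,600 |
| 15 | 3,000 | 4,500 |

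A lower end of 3,000 needs 3,000/200 = 15 groups, and an upper end of 3,300 needs 3,300/300 = 11. No single count gives both.

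**Step 3. What 3,000 requires in 11 groups.**
- Equal groups: 3,000/11 = 272.7, or about 273 per group.
- Unequal groups: for example 8 × 300 + 3 × 200 = 2,400 + 600 = 3,000.

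**Step 4. Do the per-stratum figures depend on the total?** The article gives no alpha or power for d and r. Two-sided alpha 0.05 and 80% power are assumed here, so the multiplier is 1.960 + 0.842 = 2.802.
- Half-width = 1.96 × √(0.25/n): 6.9% at n = 200 and 5.7% at n = 300.
- d = 2.802 × √(2/n), with n per group: 0.280 at 200 and 0.229 at 300.
- r = tanh(2.802/√(n − 3)): 0.197 at 200 and 0.161 at 300.

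All six figures agree with section 2.6 after rounding. They use only the stratum size, so the error in the total does not reach them. They also show that the paragraph treats 200 as a real planning floor.

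**The case against.** The best defence is that 200–300 describes a spread across groups of unequal availability. Section 2.6 bases study size on feasible recruitment and on the survey company's past performance. If most groups filled to 300 and a few reached only 200, the total would be 3,000, as in the example of 8 and 3 groups above. This stands in part: 3,000–3,300 lies inside the attainable range of 2,200–3,300, so the stated total is unexplained rather than impossible. But the article states no unequal targets, and it presents the total as the result of the per-group range. The other ways to reach 3,000 are not in the text either. Taking 10 to 11 groups at 300 gives 3,000–3,300 but leaves the stated 200 with no role. No inflation is stated. Counting one person in two diagnostic groups would lower the total, not raise it.

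It is also fair to say that the target is pragmatic and that no analysis rests on the total. That stands, and it limits the importance of the point.

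Three stronger readings are tempting, and the article does not support them.
- A reader might infer that the abstract contradicts section 2.6. It does not: 3,300 is 11 × 300, the top of the stated range.
- A reader might take "These quotas will be applied flexibly in groups with limited numbers of registered panel members" as loosening the group targets. That sentence follows the minimum quotas by age decade and concerns those.
- A reader might infer that d and r are overstated because section 2.7 will "apply pre-specified multiple comparison correction strategies that differ by sub-study". Section 2.6 offers them as approximate context for the range, not as power for the corrected tests. Sub-study 1c, which compares each disorder with controls, plans no test of a mean difference, and sub-study 1b correlates measures among patients with mental disorders, not within one stratum.

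**Conclusion.** The lower bound of the overall enrolment target is wrong as written. With the 11 groups of section 2.2, 200–300 per group gives 2,200–3,300, so the stated 3,000 is 800 too high for the stated floor of 200. The upper bound is right.

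This rests on two things: the count of 11 recruitment groups, which the exact match at 3,300 supports, and the plain reading that one range applies to every group. If unequal targets were intended, the fault is that they are not stated.

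The consequence is modest. The per-stratum precision and detectable effects stand as printed, and no planned analysis is invalidated. The correction is still worth making, because the article fixes the recruitment target in advance and its two minimum figures do not agree.

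**What to change.** Choose one of the following in section 2.6:
1. If 200 per group is the floor, give the overall target as 2,200–3,300 (11 groups × 200–300), with 3,300 as the maximum.
2. If 3,000 overall is the floor, give an average per-group target of about 273–300, or list unequal group targets that sum to 3,000–3,300.

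In either case, state the number of groups next to the total so that the product can be checked. The abstract's 3,300 can stay as the maximum. Under the second option with about 273–300 in every group, the half-widths, d and r quoted at 200 should be recalculated at the new floor. At 273 they are 5.9%, 0.24 and 0.17, on the same assumed alpha and power.

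The cost is a sentence or two of text. The analyses do not change. The first option needs no additional participants, and the second only makes explicit a floor that section 2.6 already states.

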### 2.7 Statistical Analysis

To minimize information bias, we will conduct logic and range checks during data cleaning. Descriptive analyses will summarize distributions, floor and ceiling effects, and reliability indices. Unless otherwise specified, analyses will use two-sided tests, apply pre-specified multiple comparison correction strategies that differ by sub-study (see **Supplementary Materials**), and control for prespecified covariates (e.g., age and sex). Prespecified subgroup comparisons and corresponding interaction tests for diagnostic strata and sex will be conducted a priori, whereas other interaction analyses will be considered exploratory. Effect sizes with 95% confidence intervals will be reported, including Cohen’s *d *and Hedges’ *g* for continuous outcomes, odds ratios from logistic regression models, and standardized *β* coefficients for regression paths. Because the panel provider supplies only complete records for both the survey and the two-week retest, analyses will be restricted to complete-case data. Additional methodological details are provided in the **Supplementary Materials**.

In Sub-study 1a of Aim 1, all the analyses will be conducted in accordance with the Consensus-based Standards for the selection of health Measurement Instruments (COSMIN) guidelines [87]. The psychometric validation of the DQ5-J will include CFA to test the a priori unidimensional structure, with EFA reserved as a follow-up if the model fit is inadequate, internal consistency indices (Cronbach’s alpha and McDonald’s omega), test–retest intraclass correlation coefficients, model fit criteria, hypothesis-driven convergent and discriminant validity testing, and receiver operating characteristic analyses.

In Sub-studies 1b–1d of Aim 1, the correlations between the psychosocial factors and QOL/psychiatric symptoms will be examined by assessing the associations among the BPBs scores, SAP, SES, the psychiatric symptoms and sleep characteristics measures, and QOL using correlation analyses, linear regression models, and logistic regression. Sub-study 1d will additionally apply multiple-group structural equation modeling with moderated mediation and latent profile analysis to characterize the coping strategies assessed by the CAS-1R [88,89,90].

For Aim 2, latent profiles integrating the sleep characteristics and psychiatric symptoms measures will be derived using uniform manifold approximation and projection embeddings in combination with multiple clustering algorithms. The optimal number of clusters will be determined according to a comprehensive clustering validation framework [91], incorporating multiple internal validation criteria. Differences in the psychological and demographic variables between the clusters will be evaluated using one-way analysis of variance (ANOVA) with Tukey’s Honestly Significant Difference (HSD) post-hoc test when assumptions are met, or the Kruskal–Wallis test with Steel–Dwass post-hoc comparisons otherwise, for continuous variables and chi-square tests for categorical variables.

For Aim 3, the analyses of measurement foundations and attitudes toward digital health technology and AI therapy will include CFA for the eTAP-J, ASSURE-HT, and ASSURE-AI scales as well as regression and ANOVA models to assess group differences. The associations among attitudes toward digital health technology (e.g., acceptance, anthropomorphism, and ethical concerns) and QOL will be examined using serial mediation models.

To assess the robustness of the main findings, prespecified sensitivity analyses will be conducted by varying the model specifications and key assumptions. Specifically, the analyses will be re-estimated using alternative scoring approaches or short-form versions of the questionnaires, varying the thresholds for categorized outcomes, allowing non-linear terms for continuous predictors, and perturbing clustering parameters. The stability of the results will be evaluated across these alternative specifications.

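### Aim 2 forms profiles on UMAP embeddings and picks their number by internal criteria, with no stated way to conclude that there are no discrete profiles

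*Protocol article*

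**What the plan says.** Section 2.7 states that the Aim 2 profiles "will be derived using uniform manifold approximation and projection embeddings in combination with multiple clustering algorithms". Table 1 lists UMAP as the dimension-reduction step and then "Clustering: Density-Based Spatial Clustering of Applications with Noise, hierarchical clustering, k-means, Gaussian mixture models". Section 2.7 sets the number of clusters by a cited validation framework "incorporating multiple internal validation criteria". It continues: "Differences in the psychological and demographic variables between the clusters will be evaluated using one-way analysis of variance (ANOVA", with Kruskal–Wallis and chi-square tests as alternatives).

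For sub-study 2a, Table 1 gives "Clustering features: Sleep measures (e.g., ISI, RU-SATED), External validators: EQ-5D-5L, SWLS". Sub-study 2b uses the same features. Sub-study 2c clusters on psychiatric symptoms, with the same two validators. Section 2.5.2 adds that the registry will "examine their associations with QOL and symptom severity".

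The article also contains safeguards:
- Table 1 labels 2a to 2c exploratory, and section 2.5 asks for caution and replication.
- Section 2.6 reads person-centred analyses by fit, convergence and stability.
- Section 2.7 perturbs clustering parameters as a sensitivity analysis.
- Full specifications are left to the Supplementary Materials.

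**The concern.** UMAP preserves local neighbourhoods and does not preserve distance or density. Gaps in the embedding can therefore be absent from the scores. Indices such as the silhouette are undefined for one cluster, so a rule that maximises them must return at least two. If the scores lie on a severity continuum, which the Introduction itself favours over discrete categories, any cut along it also separates other variables that follow the same gradient. EQ-5D-5L and SWLS plausibly do.

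At stake is whether 2a to 2c can tell profiles from slices of a continuum. The Discussion expects registry-derived profiles to inform clinical assessment and policy.

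**Working it through.** **The plan's own figures.** The article gives no error rate or power for the clustering. Its general figures in section 2.6 reproduce at two-sided 5% and an assumed 80% power (1.960 + 0.842 = 2.802):
- Half-width 1.96·√(0.25/n): 6.93% at n = 200, 5.66% at n = 300 (stated 6.9, 5.7).
- d = 2.802·√(2/n): 0.280 and 0.229 (stated 0.28, 0.23).
- r = tanh(2.802/√(n−3)): 0.197 and 0.161 (stated 0.20, 0.16).

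**Inputs from the article.** UMAP, the four algorithms, internal criteria, ANOVA between clusters, "External validators: EQ-5D-5L, SWLS", two-sided testing, and 200 to 300 per stratum.

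**Assumptions, not in the article.**
- Data with no clusters: x = λf + √(1−λ²)e for 8 scales, f and e normal.
- Validator: v = −ρf + √(1−ρ²)u.
- λ = 0.65 or 0.4; ρ = 0.45, 0.3 or 0.2. Feature-validator correlations are then λρ in size: 0.65 × 0.45 = 0.29, 0.65 × 0.2 = 0.13, 0.4 × 0.3 = 0.12.
- UMAP with 15 neighbours and minimum distance 0; DBSCAN settings also assumed; test level 0.05.

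**Step 1: number of clusters** (n = 300, λ = 0.65, 100 runs).

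| Rule | On UMAP | On raw scales |
|---|---|---|
| Gaussian mixture by BIC, k = 1 allowed | k = 1 in 0/100 (k from 2 to 8) | k = 1 in 100/100 |
| DBSCAN, two or more clusters | 65/100 | 0/100 |
| Mean best silhouette (k-means, Ward, mixture) | 0.53 to 0.56 | 0.17 to 0.25 |

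By silhouette, k-means, Ward and the mixture always gave two or more on the embedding, as the index requires; k = 2 was chosen in 98%, 94% and 88%. In 25 further k-means runs per setting, Calinski–Harabasz chose anything from 2 to 8.

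A second set of 30 runs (λ = 0.7, n = 500 or 1,600) gave the same contrast: BIC chose one cluster on raw scores in 30/30, and 3 to 7 on UMAP in 30/30.

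**Step 2: comparison on a validator.** ANOVA was significant in 100% at ρ = 0.45 (n = 300 and n = 600), 76% at λ = 0.4 with ρ = 0.3, and 68% at λ = 0.65 with ρ = 0.2. A variable unrelated to the factor was significant in 7% to 10%, near nominal. All 8 features differed in 100% at λ = 0.65.

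This is what slicing a continuum should give. The two halves of a normal factor differ by 2√(2/π) = 1.596 SD, so the validator differs by 1.596ρ. At ρ = 0.2 that is 0.32 SD. With 150 per half, the detectable difference at 80% power is 2.802·√(2/150) = 0.32. A perfect halving would therefore be significant about 80% of the time; the noisier clusters gave 68%.

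**Step 3: stability** (k-means, new seed, neighbours 15 to 30). At λ = 0.65 the same k returned in 100% of runs, with mean adjusted Rand index 0.86 (n = 300) and 0.88 (n = 600). At λ = 0.4 the figures were 80% and 0.67.

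**Step 4: a remedy.** The observed best silhouette was compared with the same pipeline run on 19 single-population Gaussian datasets with the observed mean and covariance. More than one profile was reported only if the observed value exceeded all 19 (nominal 5%). With no clusters this happened in 2 of 20 datasets. At a true 5%, two or more in 20 has probability 1 − 0.95²⁰ − 20·0.05·0.95¹⁹ = 1 − 0.358 − 0.377 = 0.26, so the result is compatible with the nominal level. With three well-separated clusters it happened in 6 of 6. Replicates are few and the true-cluster case was easy.

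**The case against.** The strongest reply is that Aim 2 is exploratory, that replication is asked for, that no confirmatory sub-study depends on it, and that the cited framework and Supplementary Materials, which are not shown, may already contain a null reference. This stands as a limit on severity and confidence. It does not remove the artefact. The label governs how firmly results are stated, and replication with the same method can reproduce a stable false split. Adding k = 1 alone would not be enough, because BIC was allowed k = 1 on the embedding and never chose it.

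A reader might infer more than the documents support:
- **That the pipeline always yields several validated profiles.** By silhouette it was mostly two. DBSCAN returned one cluster in 35 of 100 runs. Validator significance depended on correlation with the features.
- **That the validator comparison is circular.** EQ-5D-5L and SWLS are clustering features in no sub-study. Overlap arises only if symptom severity or other psychological variables are tested where they also formed the clusters, as could happen in 2c.
- **That section 2.5.2 contradicts Table 1.** It allows either domain or both. The mismatch is with section 2.7 alone, which describes profiles combining sleep and psychiatric symptom measures, and that may be a loose summary of three sub-studies.
- **That the article offers ANOVA as proof that clusters exist.** It speaks of group comparisons, though it does call the two scales validators.

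**Conclusion.** The point holds at moderate severity. As described in the article, Aim 2 forms profiles in a space that can create separation, chooses their number by criteria that typically cannot return one, and then relies on comparisons and stability checks that a false split can pass. On single-population data the embedding turned a one-cluster answer (100/100 by BIC) into two or more (100/100). A correlated validator then differed in 68% to 100% of runs.

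These figures rest on assumed loadings, validator correlations and software settings. The raw-against-embedded contrast and the DBSCAN rate were obtained at loadings of 0.65 or 0.7 (DBSCAN at 0.65 only). At loading 0.4 the stability check was weaker but still returned the same k in 80% of runs.

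It would go too far to say that the output would look the same whether or not profiles exist. In the few datasets with true, well-separated clusters, the reference comparison told the two situations apart. Whether UMAP should ever precede clustering, and whether a profile must predict beyond the continuous scores to be useful, are matters on which statisticians differ. The conclusion needs neither.

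**What to change.** 1. Run the identical pipeline on simulated single-population data with the observed covariance. Report more than one profile only if the observed index exceeds that reference.
2. As a required sensitivity analysis, confirm the solution in the standardised original scores with a model that allows k = 1, for example a Gaussian mixture with BIC.
3. Reconcile the Aim 2 paragraph of section 2.7 with the Table 1 feature lists (sleep for 2a and 2b, psychiatric symptoms for 2c). Treat comparisons on clustering features as descriptive, and keep inferential tests for non-feature variables such as EQ-5D-5L and SWLS.

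If the Supplementary Materials or the cited framework already provide item 1 or 2, one sentence in section 2.7 saying so is enough. The cost is wording and modest computing, with no change to data collection. The downside is that the result may be that no discrete profiles are supported.
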